### Withdrawal of participants from treatment

Participants may withdraw from the study for any reason or at any time. The investigators may also withdraw participants from the study if there are concerns about their safety and/or if they are unwilling or unable to comply with study procedures. The criteria for discontinuing EMDR treatment include the following: the participant does not attend for more than three consecutive treatments or for more than four treatments in total; serious adverse events (defined in the next section); participant request; and Data Monitoring Committee recommendation (described in the next section). As already described, we will analyze participants using intention-to-treat methods.

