### Randomization, allocation concealment, and blinding

Consenting participants will receive the pre-treatment (T0) measurements. After T0, participants will be randomly assigned to either the EMDR or treatment as usual group. An independent research manager at the District Health Board research office (who is not involved in the study) will generate the random sequence. This allocation sequence will be computer-generated and non-stratified with varying block sizes, which will not be disclosed to the researchers to ensure concealment. After randomization, the research office will notify the trial coordinator from the research team as to the allocation. To ensure allocation concealment, the randomization code will not be released until after the participant has been recruited into the trial, which takes place after all baseline measurements have been completed.

After allocation, the participants will be informed which group they are in. Hence, neither the participants nor the specialized therapists who deliver EMDR will be blinded to the allocation (as it is not practical to undertake blinded EMDR). However, outcome assessors will be blinded to treatment allocation, as will those performing data entry and the trial statistician (MW). Assessors and therapists will emphasize the importance of blinding to the participants and remind them not to reveal the randomized treatment condition. Assessors will avoid contact with the therapists and other caregivers. Assessors will be asked to report any case of unblinding, in which case, another assessor will repeat the entire measurement.

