To promote participant retention and adherence, we will present information about the study to health professional and patient groups before and during the study, to promote and sustain interest in the trial. We will enlist key worker (case manager) support to remind participants to attend treatment sessions and the follow-up assessments. The therapist and assessors will travel to the site where the participant is residing, to reduce logistical barriers to attending. The EMDR therapist will complete a record of attendance.

Randomized participants who discontinue treatment will have T1 and T2 assessments completed if possible. Once a participant is enrolled, the investigators will make every reasonable effort to follow them up for the entire study period.

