### Trial monitoring and oversight

The risks of the study are thought to be low based on previous research, which has found EMDR to be safe, effective, and well tolerated in people with serious mental illness. However, the population is vulnerable so there are a number of safeguards in place. A Data Monitoring Committee (DMC) has been set up as an advisory body responsible for monitoring emerging safety and efficacy data, reviewing trial conduct and making recommendations. The DMC is independent of the study organizers and funders. Its membership is multidisciplinary and comprises the Clinical Director (Chair) and Operations Manager from the Central Regional Forensic and Rehabilitation Service, a senior psychologist not related to the study, and the principal investigator. During the recruitment period, interim analyses will be supplied in strict confidence to the DMC, together with any analyses the DMC may request.

The base rate of serious events in this population is much higher than in the general population, and it may be difficult to establish whether such events are related or unrelated to therapy. All serious adverse outcomes will be reported immediately to the DMC. We have predetermined that any serious event such as a serious deliberate self-harm attempt (requiring medical attention), an assault on another person (requiring medical attention), or a return to an environment of high security will be a reason for the participant being withdrawn from the study. Any other significant adverse effects will be discussed on a case-by-case basis. The DMC and research team will formally review the feasibility and safety of the study after data have been collected on 10 participants, before further participants are recruited.

The terms of reference of the DMC are available on request from the principal investigator.

In the unlikely event that someone is harmed in the course of the trial, they would be eligible under New Zealand law to apply for compensation from the Accident Compensation Corporation. This is explained in the informed consent process.

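### Investigators may withdraw non-compliant participants from the study, which conflicts with following every enrolled participant and with intention-to-treat analysis, and could bias the EMDR comparison if used on poor attenders

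*Protocol article*

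**What the plan says.** Withdrawal of participants from treatment contains two different rules. The first is at study level and discretionary: investigators may "withdraw participants from the study if there are concerns about their safety and/or if they are unwilling or unable to comply with study procedures". The second is a list of reasons to stop EMDR, one of which is that "the participant does not attend for more than three consecutive treatments or for more than four treatments in total". The section closes: "As already described, we will analyze participants using intention-to-treat methods". Quantitative data analysis also specifies intention to treat.

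The follow-up commitment is at the end of Secondary outcome measurements: "Randomized participants who discontinue treatment will have T1 and T2 assessments completed if possible". It continues: "Once a participant is enrolled, the investigators will make every reasonable effort to follow them up for the entire study period".

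On knowledge of allocation, the randomization section says "neither the participants nor the specialized therapists who deliver EMDR will be blinded to the allocation", and that after randomization "the research office will notify the trial coordinator from the research team as to the allocation". Assessors, data-entry staff and the statistician are blinded.

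The waiting list starts treatment only at T2 (Outcome measures). Before then it has assessments only, while the EMDR arm has the same assessments plus nine sessions.

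**The concern.** The section heading concerns treatment, but the compliance clause concerns the study. The next sentence deals separately with stopping EMDR, so the text itself treats leaving the study and stopping treatment as different things, and it puts non-compliance under leaving the study. The explicit T1 and T2 safeguard covers those who discontinue treatment. Nothing says that a participant withdrawn from the study by an investigator is still assessed.

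At stake are the primary outcomes of anyone removed under the clause. No analysis plan can recover CAPS or PSS-SR scores that were never collected. The mixed model and multiple imputation, in their usual missing-at-random form, predict removed EMDR participants largely from EMDR participants who stayed. If those removed gain less, the estimate drifts from the effect of being offered EMDR towards the effect in those who comply.

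**Working it through.** **Passages side by side.** Loss despite reasonable effort fits the follow-up commitment, which is qualified on purpose. Loss because an investigator chooses to end participation for non-compliance does not fit it, and does not fit intention to treat either. Two links are conditional:

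- Missed sessions have their own rule, which stops EMDR and leaves T1 and T2 in place. A poor attender loses outcome data only if the general clause on study procedures is also applied.
- If it is applied to session attendance, only the EMDR arm is exposed to it before T2. If it covers only consent and assessments, both arms are exposed.

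**The plan's own figures** (Sample size calculations: difference 16, SD 16, two-sided 0.05, power 0.80). The normal formula gives n = 2(1.960 + 0.842)² × (16/16)² = 15.7 per arm, so 16; the exact t test gives 17. The stated 15 is close. With 30% dropout, 16/0.7 = 22.9, which matches the stated 23, and 23 × 0.7 = 16.1 remain. These figures are not in dispute and are used only for scale.

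**Possible inflation.** Let w be the share of EMDR non-compliers and e their own benefit, with 16 points of benefit in compliers. The documents give neither w nor e, so both are assumptions.

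- Effect with everyone kept: 16(1 − w) + e·w
- Effect if all non-compliers are removed and treated as similar to those who stayed: 16
- Inflation: w(16 − e)

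| w | Effect, e = 0 | Inflation | Effect, e = 8 | Inflation |
|---|---|---|---|---|
| 10% | 14.4 | 1.6 | 15.2 | 0.8 |
| 20% | 12.8 | 3.2 | 14.4 | 1.6 |
| 30% | 11.2 | 4.8 | 13.6 | 2.4 |

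For scale, 20% of 23 is about five people. The standard error with 16 per arm is 16 × √(2/16) = 5.66, so 3.2 points is 0.57 of a standard error, or 0.20 SD.

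**No true effect.** A simulation had 23 per arm, removed non-compliers from the EMDR arm only, and used a t test on the remaining scores. The expected spurious difference is w times the prognosis gap.

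- Non-compliers 8 to 16 points worse, w of 10% to 30%: 0.8 to 4.8 points in favour of EMDR, with two-sided type I error of about 0.05 to 0.13.
- Same prognosis: no bias.
- Non-compliers 8 points better: the bias reverses, −0.8 to −2.4 points.

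The planned model adjusts for baseline and could absorb part of a prognosis gap, so these figures describe the unadjusted case.

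**The case against.** A reader might infer that the protocol has unblinded investigators removing poor attenders from the EMDR arm and so inflating the effect. The documents do not support that:

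- Non-attendance has a specific rule that stops EMDR only, and treatment discontinuers keep T1 and T2 where possible. The compliance clause is permissive and general, and can be read as covering consent and assessments in both arms.
- The text does not say who decides on withdrawal. That the decision-maker may know the allocation is an inference from the blinding section.
- The text does not say that assessment ends after an investigator withdrawal. It leaves this open, beside an intention-to-treat promise.
- The sizes above assume that every non-complier is removed, although removal is discretionary. The plan's 30% allowance is attributed to discharge, address change and loss to follow-up, and lower dropout is expected (about 18% in a meta-analysis, below 15% in the team's own research). It is not an estimate of non-compliance.
- Last observation carried forward is planned, with missing loss of diagnosis counted as no loss. Take the means cited in Sample size calculations (baseline 69.9, EMDR 40.3, waiting list 56.5), with 20% of the EMDR arm removed before T1 and no benefit in them. Carrying baseline forward gives 56.5 − (0.8 × 40.3 + 0.2 × 69.9) = 10.3 points, below the effect with everyone kept, 0.8 × 16.2 = 13.0. A gap between this and the main result would be visible.

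All of this stands, and it makes the bias conditional. It does not remove the conflict. The carried-forward analysis is a robustness check that errs in the other direction here, so it could signal a problem without supplying the right estimate. The qualified wording on follow-up excuses unavoidable loss, not loss by choice.

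**Conclusion.** The conflict is real: a study-level withdrawal for non-compliance cannot stand beside the effort to follow all enrolled participants and an intention-to-treat analysis. The bias is possible, not established. It requires that the clause be applied to session attendance, that outcome collection then stops, and that those removed do worse or benefit less than the rest. Given all three, with 10% to 30% non-compliers all removed, the main estimate would be too large by 0.8 to 4.8 CAPS points against a planned 16. Without the third condition it is unbiased or biased the other way. The protocol should be corrected because the missing outcomes could not be recovered later, but nothing in it shows that removals will be one-sided or made with knowledge of the allocation.

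**What to change.** Reconcile Withdrawal of participants from treatment with the follow-up sentences and with Quantitative data analysis. Remove non-compliance as a ground on which investigators may end outcome collection. State that T1 and T2 assessments continue for anyone who stops EMDR or does not comply, unless the participant withdraws consent to follow-up. The criteria for discontinuing EMDR are left unchanged.

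The cost is about one sentence of protocol text. No visits are added, because T1 and T2 are already planned for those who discontinue treatment. The downside is some assessor effort in pursuing poorly engaged participants. Recruitment was still under way according to Trial status, so the change could still protect data.

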### Trial monitoring and oversight

The risks of the study are thought to be low based on previous research, which has found EMDR to be safe, effective, and well tolerated in people with serious mental illness. However, the population is vulnerable so there are a number of safeguards in place. A Data Monitoring Committee (DMC) has been set up as an advisory body responsible for monitoring emerging safety and efficacy data, reviewing trial conduct and making recommendations. The DMC is independent of the study organizers and funders. Its membership is multidisciplinary and comprises the Clinical Director (Chair) and Operations Manager from the Central Regional Forensic and Rehabilitation Service, a senior psychologist not related to the study, and the principal investigator. During the recruitment period, interim analyses will be supplied in strict confidence to the DMC, together with any analyses the DMC may request.

The base rate of serious events in this population is much higher than in the general population, and it may be difficult to establish whether such events are related or unrelated to therapy. All serious adverse outcomes will be reported immediately to the DMC. We have predetermined that any serious event such as a serious deliberate self-harm attempt (requiring medical attention), an assault on another person (requiring medical attention), or a return to an environment of high security will be a reason for the participant being withdrawn from the study. Any other significant adverse effects will be discussed on a case-by-case basis. The DMC and research team will formally review the feasibility and safety of the study after data have been collected on 10 participants, before further participants are recruited.

The terms of reference of the DMC are available on request from the principal investigator.

In the unlikely event that someone is harmed in the course of the trial, they would be eligible under New Zealand law to apply for compensation from the Accident Compensation Corporation. This is explained in the informed consent process.

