## Study aims

### Primary aim

In a sample of people receiving forensic and rehabilitation mental health care, we aim to examine: the efficacy of EMDR versus the waiting list for treating PTSD symptomology; and the safety and acceptability of EMDR versus the waiting list as indicated by adverse events.

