Health condition(s) or problem(s) studied	PTSD in people receiving care from forensic mental health services
Intervention(s)	EMDR therapy
Key inclusion and exclusion criteria	Inclusion criteria: aged 18–65 years; a lifetime history of a psychotic disorder or a mood disorder with psychotic features as diagnosed according to ICD-10 or DSM-5 criteria; meeting diagnostic criteria for PTSD (Clinician Administered PTSD Scale (CAPS)); current patient of the forensic and rehabilitation mental health services; competent to provide informed consent; likely to remain in the area for the 6-month trial duration (i.e., if a prisoner, release date at least 6 months away; if a patient within a forensic mental health service, their anticipated discharge is at least 6 months away) Exclusion criteria: high suicidality, operationalized as the combination of having a high suicidality score on the Mini International Neuropsychiatric Interview (MINI-plus) or with a suicide attempt within the past 6 months; mental state considered by the treating psychiatrist as too unstable to participate in the trial (participants may be experiencing chronic low-grade symptoms, but cannot be acutely psychotic); insufficient competence in the English language to understand, provide informed consent, and participate in therapy and data collection
Study type	Single-blind, randomized controlled trial
Date of first enrolment	25 May 2018
Target sample size	46
Recruitment status	Currently recruiting
Primary outcome(s)	Change in PTSD symptoms (measured by the CAPS and PSS-SR), treatment safety (measured by the adverse event questionnaire), and acceptability of the EMDR treatment (measured by the TAAS and by qualitative participant feedback)
Key secondary outcomes	Posttraumatic cognitions (PTCI), self-disturbance (TSI-2 Factor 1), posttraumatic stress (TSI-2 Factor 2), externalization (TSI-2 Factor 3), somatization (TSI-2 Factor 4), depression (BDI-II), psychosis (PSYRATS), overall functioning (WHODAS 2.0), social functioning (Social Functioning scale), self-esteem (RSES)

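### A serious adverse event triggers withdrawal from the study in one section but only from EMDR in another, so the primary safety questionnaire can go missing because of the events it records

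*Protocol article*

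**What the plan says.** All references are to the protocol article.

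- **Trial monitoring and oversight.** Serious self-harm or an assault on someone else, each needing medical attention, or a "return to an environment of high security will be a reason for the participant being withdrawn from the study". The rule is described as decided in advance. Only other significant adverse effects are left to case-by-case discussion. The rule names no arm. Serious adverse outcomes go to the DMC at once.
- **Withdrawal of participants from treatment.** This section first covers leaving the study: "The investigators may also withdraw participants from the study if there are concerns about their safety". It then turns to stopping therapy: "The criteria for discontinuing EMDR treatment include the following". That list contains "serious adverse events (defined in the next section"), and the next section is Trial monitoring and oversight. It closes by affirming intention-to-treat analysis.
- **Secondary outcome measurements (closing paragraphs, on retention).** "Randomized participants who discontinue treatment will have T1 and T2 assessments completed if possible". Also: "Once a participant is enrolled, the investigators will make every reasonable effort to follow them up for the entire study period".
- **Primary aim.** One of the two parts is "the safety and acceptability of EMDR versus the waiting list as indicated by adverse events".
- **Table 2, primary outcomes.** These include "treatment safety (measured by the adverse event questionnaire").

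**The concern.** The same class of event leads to two different instructions. Under one, EMDR stops and the participant is still assessed at T1 and T2. Under the other, the participant leaves the study, and nothing says assessments continue.

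The difference matters because of what the AEQ measures. It asks about self-harm, attempted suicide, hurting others and a move back to higher security, which overlaps the withdrawal triggers. The only other adverse-event scale is given around EMDR sessions two and three, so the AEQ is the only adverse-event instrument described that both arms share. If the study-withdrawal rule is applied, AEQ data are missing because of the events the AEQ should record. A between-arm safety comparison based on the remaining questionnaires would then be incomplete in a way related to the outcome itself.

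**Working it through.** **1. The rules side by side**

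| Section | Trigger | Consequence |
|---|---|---|
| Trial monitoring and oversight | Serious event (examples listed) | Reason for withdrawal from the study |
| Withdrawal of participants from treatment | The same events, by cross-reference | Criterion for stopping EMDR |
| Secondary outcome measurements, retention paragraphs | Treatment stopped for any reason | T1 and T2 assessed if possible |
| Same | Enrolment | Every reasonable effort at follow-up for the full period |

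The first row cannot be read as the second simply by taking study to mean treatment. The withdrawal section itself uses the two terms for different things. The first row also applies to waiting-list participants, who have no EMDR to stop, because their treatment starts at T2 (note to Fig. 2).

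**2. What is lost**

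The outcome measures are taken at T0, T1 (10 weeks) and T2 (6 months).

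- Event before T1, then withdrawn: no T1 or T2 AEQ, CAPS or PSS-SR.
- Event after T1, then withdrawn: T1 intact, T2 lost.

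The methods for missing data in Quantitative data analysis would not readily recover the missing AEQ. Carrying the last observation forward would use the pre-randomisation value, and multiple imputation would draw on participants who were not withdrawn.

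**3. How many participants**

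The target is 46, so 46 / 2 = 23 per arm (Sample size calculations). The same section allows 30% attrition: 0.30 × 23 = 6.9 per arm. The protocol describes the base rate of serious events as high but gives no figure, so a trigger risk of 5–20% by T1 is assumed.

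| Assumed risk by T1 | All withdrawn | Half withdrawn |
|---|---|---|
| 5% | 0.05 × 23 = 1.15 (about 1.2) | 0.5 × 1.15 = 0.58 (about 0.6) |
| 20% | 0.20 × 23 = 4.6 | 0.5 × 4.6 = 2.3 |

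All four values are below 6.9.

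**4. Effect on the AEQ comparison (illustration only)**

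Let p be the true risk of a trigger event and s the share of participants with an event who still complete the AEQ. The risk seen among AEQ completers is p·s / [1 − p(1 − s)]. Assume true risks of 20% and 10%.

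- s = 1: 20% and 10%, difference 10 points.
- s = 0.5: 0.10 / 0.90 = 11.1% and 0.05 / 0.95 = 5.3%, difference 5.8 points.
- s = 0: 0% and 0%, difference 0.

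The last line is the extreme. It needs every affected participant to leave before the next AEQ and takes no account of reports to the DMC.

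**The case against.** The best defence is that the wording is loose and the intent is clear. The withdrawal section is headed as being about treatment yet opens with leaving the study, so the authors do mix the terms. Its cross-reference can be read as making the listed events treatment-stopping criteria. The follow-up commitment has no exception for serious events and covers everyone enrolled, and intention-to-treat is affirmed. The phrase about being a reason for withdrawal also falls short of saying that withdrawal is automatic.

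That reading is plausible as intent, but it does not settle the text. The rule is fixed in advance and reserves discretion for other effects. It also applies to the waiting-list arm, where stopping EMDR has no meaning before T2. Staff could reasonably act on either instruction.

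Several further points limit the size of the concern, and they stand:

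- Serious events reach the DMC immediately, so the triggering event is not unrecorded. What is lost is the AEQ and the participant's other later outcomes.
- The AEQ looks back only two months, so even with full follow-up it misses events between T1 and roughly month four. That gap does not restore the T1 and T2 data lost through withdrawal.
- The overlap is partial. AEQ items are wider than the withdrawal triggers and include alcohol, drugs, crisis help and reoffending.
- Follow-up after treatment stops is promised only where possible.
- The event rates above are assumed.

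**Conclusion.** The contradiction is real and should be fixed. As written, a predetermined rule can remove participants from follow-up because of the events that a primary safety measure is meant to record.

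Under an assumed 5–20% trigger risk by T1, between 0.6 and 4.6 participants per arm of 23 would have an event but no T1 AEQ, depending on whether half or all are withdrawn. In arms this small, a few uncounted events could alter the safety comparison. The losses fit within the attrition allowance, so no loss of power is claimed. With no event rate by arm, the size and direction of any effect on CAPS or PSS-SR cannot be stated, and none is claimed. The finding concerns safety capture only.

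**What to change.** Amend the sentence in Trial monitoring and oversight so that a serious event may lead to discontinuing EMDR, with T1, T2 and adverse-event collection continuing in both arms unless the participant withdraws consent to follow-up. This brings it into line with the treatment-discontinuation list and the retention paragraphs. The separate power to withdraw someone from the study over safety concerns should carry the same provision for continued data collection.

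The cost is a one-sentence amendment and matching consent wording. The visits are already scheduled, and assessors already plan to travel to where participants live. The practical burden is some extra effort to assess people moved to higher security.
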